## 6.1 Assessments and Procedures

See schedule of events table, 3.2 for overview

### Enrolment/Baseline

Screening, and patient information: Preoperatively, patients will be screened by the surgeons/anesthesiologists for inclusion and exclusion criteria. If suitable for inclusion, the patients will be given verbal and written information about the study and allowed to ask questions then or prior to randomization. No patient will be included in the study unless written informed consent is obtained. Demographic data will be recorded and routine blood samples drawn. This visit will take an additional 15-30 min and does not imply an extra visit to the hospital but be a part of the Surgical and/or Anesthetic consultation. QoR-15: A questionnaire - QoR-15- will be completed by the patient.

### Day of surgery

Randomization: Will be performed on the morning of surgery and drugs (Ropivacaine or normal saline) prepared by personnel who will not participate in the study.

Perioperative recordings will be made on a standardized Case Record Form (CRF) that includes drugs administered and monitoring performed. All side effects, the operative report, complications and SAE during or after surgery will be recorded.

### **Postoperative day 1**

Routine clinical blood-samples will be drawn.

### **Postoperative day 3**

In addition to routine clinical management including blood samples. QoR-15 will be completed by the patient. Postoperative morbidity score (POMS) will be recorded. The intraperitoneal catheter will be extracted. All adverse events and SAE after surgery will be recorded.

### **Postoperative day 5**

In addition to routine clinical management including blood samples POMS and Adverse events will be registered. All adverse events and SAE after surgery will be recorded

### **Postoperative day 30**

Complications including readmissions as assessed by the C-D classification, length of hospital stay, number of days with Epidural catheter will be recorded. All adverse events and SAE after surgery will be recorded. The final histopathology will be recorded.

### **~ 6 months postoperatively**

The primary endpoint time from surgery to start of chemotherapy will be recorded including type and frequency of adjuvant treatment as decided by the double blinded attending medical oncologist. All adverse events and SAE after surgery will be recorded

### **3-years after surgery**

The medical records will be reviewed for vital status. Date of death (if applicable) will be recorded.

### **5-years after surgery**

The medical records will be reviewed for vital status. Date of death (if applicable) will be recorded.

## **7 Translational research component**

The study will include a translational research component at site Karolinska only, which will have its focus on examining peritoneal response to surgical trauma and local anesthetics. Specifically, mesothelial chemotherapy resistance and inflammation, cell-free tumour DNA and inflammation in blood. The translational studies will be performed blinded for the investigators upon prospectively collected biopsies from the peritoneum at time of surgery

and blood (collected at several time-points during the study), see schedule of events table, 3.2.

## 8 Statistical considerations

### 8.1 Primary endpoint

Time (days) to start of adjuvant chemotherapy after cytoreductive surgery

### 8.2 Secondary endpoints

Postoperative complications, postoperative morbidity, quality of recovery, cardiac and renal impairment and overall survival

### 8.3 Data analyses

The primary endpoint, time to start of adjuvant chemotherapy will be analyzed using a linear regression model including the variable treatment. Results will be presented as the mean difference in days together with 95% confidence intervals and a Wald-test p-value. The significance level in the main analysis is set to 5%. Regression models including different clinical factors will also be estimated to take potential confounding into account. All analyses of primary and secondary outcome will be performed according to the intention-to-treat principle but may also be presented as per-protocol. For safety data, patients will be analyzed according to per-protocol approach.

Differences in complications, morbidity and in cardiac and renal impairment will be tested using Chi-square tests of independence. For dichotomous outcomes result will also be presented as differences in proportions together with 95% confidence intervals. Overall survival time will be calculated from the date of randomization to the date of death. For patients still alive, survival time will be calculated from the date of randomization to the date of last visit. Results from the survival analysis will be graphically presented as Kaplan-Meier curves. Proportional hazards regression models will be used to estimate the effect of the intervention on time to death. Results will be presented as hazard ratios 95% confidence intervals and Wald test p-values.

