There is a theoretical risk of catheter-related abdominal infection, however, in our small pilot study we had no catheter related infection. Since the abdominal catheter is inserted under sterile conditions during surgery and a bacterial filter is always used when injecting LA, we do not anticipate any additional risks for participants. However, the patients will be followed-up closely to detect any evidence of infectious complications and start antibiotic management early, if a catheter-related infection is suspected.

In summary, and if our hypothesis is proven correct, it is very much to the advantage for women with advanced EOC subjected to surgery to administer LA, since it may lead to earlier recovery and start of adjuvant chemotherapy. The administration of LA is easy and Ropivacaine is a cheap drug with low toxicity and very few known side effects. The benefits of LA intraperitoneally, if proved, far outweigh the small risk (if any) of systemic toxicity.

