## 12 Proceedings for Adverse Events

### 12.1 Definition of Adverse Events

An Adverse Event (AE) is any untoward medical occurrence in a subject administered Investigational Medicinal Product (IMP) and which does not necessarily have a causal relationship with this product. An AE can be any unfavorable and unintended sign, abnormal laboratory finding, symptom or disease temporally associated with the use of IMP, whether or not related to the product. The AE are reported during ongoing study treatment.

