#### 12.1.2 Definition of Serious Adverse Events

Each AE is to be classified by the investigator as serious or non-serious. Seriousness is not defined by a medical term; it is a result or an outcome. An AE is defined as a Serious Adverse Event (SAE) if it:

- results in death
- is life-threatening
- requires inpatient hospitalization or prolongation of existing hospitalization
- results in persistent or significant disability/incapacity
- results in a congenital anomaly/birth defect
- other medically important event

The SAE are reported up to 30 days after end of study treatment (33 days postoperatively)

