## 12.4 Adverse Events

### 12.4.1 Reporting of Adverse Events (AEs)

All AEs will be recorded on a separate AE form in the CRF. The following information will be recorded:

- Description of the event.
- Date of onset.
- Date of resolution (or that the event is ongoing).
- Action taken as a result of the event.
- Seriousness of the event.
- Severity of the event.
- Outcome of the event.
- Investigator's assessment of relationship to study medication.

Postoperative pain will be documented and analyzed but will not be registered as an AE.

Physiological variations related to anesthesia or surgical procedures, postoperative complications, will be recorded but not analyzed as an AE.

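### Safety data are assigned to a per-protocol set that is not defined, and the sections that set the window for non-serious adverse events contradict each other

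*Protocol*

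**What the plan says.** Section 8.3 names two analysis populations. For efficacy: "All analyses of primary and secondary outcome will be performed according to the intention-to-treat principle but may also be presented as per-protocol". For safety, in the next sentence: "For safety data, patients will be analyzed according to per-protocol approach". Neither population is defined anywhere in the protocol. Section 4.6 allows the investigator or sponsor to end a woman's participation because of unacceptable adverse events or reactions, or because she does not follow study procedures. Her later follow-up is then by clinic routine.

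On the window for adverse events, section 12.1 says: "The AE are reported during ongoing study treatment". Section 12.1.1 says the same for adverse reactions (ARs). Study treatment ends 72 hours after surgery (section 5.1). The ~6 months entry in section 6.1 says: "All adverse events and SAE after surgery will be recorded". The schedule in section 3.2, the other visit entries in section 6.1, and section 12.3 give further time points, set out below. Section 12.4.1 adds: "Physiological variations related to anesthesia or surgical procedures, postoperative complications, will be recorded but not analyzed as an AE".

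**The concern.** A safety analysis should count harm among everyone exposed. A set chosen for adherence tends to lose women whose exposure was cut short by the harm being measured. The protocol has not left this choice to a statistical analysis plan: section 8.3 makes it, with a term that points the wrong way.

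The second problem is one of capture. If one section limits AE reporting to ongoing treatment and another asks for all AEs months later, two sites can follow the protocol correctly and produce different AE counts for similar patients. At stake are the AE rates in a trial whose section 13 anticipates routine use of the treatment if the hypothesis is confirmed. The primary endpoint is not affected.

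**Working it through.** **The safety set.** Two consecutive sentences of section 8.3 use the same term. In the first, per-protocol is the optional alternative to intention-to-treat. In the second, it is the only approach for safety. Nothing suggests a change of meaning, and nothing equates it with treatment received. Section 4.6 shows that stopping for harm is foreseen, so women who could fall outside an adherence-based set are expected to exist.

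One group of outcomes falls under both rules. Section 2.5 lists complications and morbidity as secondary outcomes, which section 8.3 analyses by intention-to-treat. Section 11.3 also lists the Clavien-Dindo grade and the Postoperative Morbidity Score (POMS) as safety assessments, which section 8.3 analyses per-protocol.

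**Size.** Let *t* be the true proportion with a treatment-limiting harm in an arm, and *s* the share of those women who stop and are excluded, with no other exclusions. The reported proportion is (*t* − *ts*)/(1 − *ts*). The arm size is 220/2 = 110 (section 8.4, with 1:1 allocation from section 4.4). The values of *t* and *s* below are assumptions; the protocol gives neither.

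| Assumed *t* | *s* = 25% | *s* = 50% | *s* = 100% |
|---|---|---|---|
| 5% (5.5 women) | 4.125/108.625 = 3.8% | 2.75/107.25 = 2.6% | 0/104.5 = 0% |
| 10% (11 women) | 8.25/107.25 = 7.7% | 5.5/104.5 = 5.3% | 0/99 = 0% |

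The table shows the direction, and that the result ranges from no change (*s* = 0) to complete loss (*s* = 100%). It is not an estimate for this trial.

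**The windows.** The one figure that can be reproduced is the SAE limit: 72 h is 3 days, and 3 + 30 = 33 days after surgery, as section 12.1.2 states. For AEs and ARs in general the sections read:

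| Section | When AEs or ARs are reported or recorded |
|---|---|
| 12.1 (AE), 12.1.1 (AR) | While study treatment is ongoing, so to 72 h |
| 3.2, AE/SAE row | Day of surgery and days 1, 3, 5 and 30 |
| 6.1, days 3, 5 and 30 | AEs and SAEs at each |
| 6.1, about 6 months | AEs and SAEs since surgery |
| 12.3 | Visits 1–11; the protocol numbers no visits |

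The schedule has 12 columns. Counted from the left, the eleventh is 3 years after surgery, so section 12.3 cannot be matched to any of the other rows. A non-serious AE on day 10 is outside the window in section 12.1 and inside the one in sections 3.2 and 6.1. A non-serious AE at month 4 is inside only the 6-month entry and possibly section 12.3. By then, adjuvant chemotherapy may be contributing to what is recorded.

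**The case against.** The strongest reply is that much of the harm is captured and analysed whatever the AE sections say. SAEs and suspected unexpected serious adverse reactions (SUSARs) are reported to day 33. Clavien-Dindo complications run to day 30, and POMS, with its infectious domain, is scored on days 3 and 5. Section 8.3 adds: "Differences in complications, morbidity and in cardiac and renal impairment will be tested using Chi-square tests of independence". Those are secondary outcomes under intention-to-treat. This stands.

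A reader of section 12.1 might infer that AE capture stops with the infusion and that harms after 72 hours disappear. The documents do not support that, because sections 3.2, 6.1 and 12.3 all collect AEs later. Section 9.1 notes that "There is a theoretical risk of catheter-related abdominal infection", and a reader might infer that such an infection after catheter removal would go uncounted. It would be recorded as a complication, and an infection that prolonged or required a hospital stay would be an SAE. What remains exposed is the non-serious AE count.

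It is also fair to say that exclusion of women who stop is an inference, since the set is undefined and as-treated may have been meant. That limits the claim to what the wording permits, but the wording would still need to change. Finally, saline is given in the same manner, so catheter problems can remove women from both arms. The between-arm difference is materially distorted only if stopping for harm differs by arm. The pilot, as section 9.1 reports it, had no signs of systemic toxicity and no catheter-related infection.

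**Conclusion.** The point holds in two parts. First, section 8.3 fixes the safety analysis on an undefined set which, on its usual meaning and its use one sentence earlier, can exclude women whose treatment was stopped because of harm. AE rates may be understated. The size cannot be computed from the documents, and a flat statement that harm in the ropivacaine arm is biased toward zero is not supported. It would need a per-protocol definition that excludes these women and a discontinuation rate by arm, and the protocol gives neither.

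Second, the AE and AR windows contradict each other across sections 3.2, 6.1, 12.1, 12.1.1 and 12.3. This rests on no assumption; it is visible on the page. The day-30 visit beside the day-33 SAE limit is not in itself a conflict. Keeping postoperative complications out of the AE tables (section 12.4.1) is not an error either, because they are analysed by arm elsewhere.

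**What to change.** In section 8.3, replace the safety sentence with: *Safety data will be analysed in all women who received any study drug (from intraoperative dose 1), according to the treatment actually received.* Taken literally, this includes any woman who received dose 1 and was then excluded under section 6 because no tumour was resected. It should be made clear that her safety data are kept.

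Reconcile sections 3.2, 6.1, 12.1, 12.1.1 and 12.3 to one window for AEs and ARs, and replace Visits 1–11 with named time points. Postoperative day 33, already the SAE limit, is one candidate. If it is chosen, note that the planning means of 26 and 31 days to chemotherapy (section 8.4) both fall before day 33, by 33 − 26 = 7 and 33 − 31 = 2 days. Recording whether an AE began before or after the first infusion would keep chemotherapy effects separable. Bringing complications into the by-arm AE tables is optional.

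The cost is wording, plus some change in AE recording depending on the window chosen. The sample size and the primary analysis are unaffected. If the change to AE collection counts as substantial, sections 9.2 and 15.7 require ethics and regulatory review.

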#### **4.6 Withdrawal criteria**

Subjects can discontinue their participation in the study at any time without any consequence to his/her continued treatment. The investigator/sponsor can at any time terminate the study for a subject due to, e.g., unacceptable adverse events/adverse reactions or because the subject does not follow procedures in the study protocol. If the subject discontinues the study, follow-up of this subject will be performed according to the clinic's routine.

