# 5 Study treatment

## 5.1 Intervention

**Group IPLA:** Ropivacaine 0.2%. After opening the peritoneal cavity and before any surgical dissection, 40 ml of the Ropivacaine will be rinsed in all quadrants within the abdominal cavity under direct vision after opening the peritoneum in order to achieve uniform spread. This will be repeated on two further occasions, first half way through the surgical procedure as estimated by the surgeon and again before closing the abdominal cavity. After the procedure is completed, a plastic multi-port catheter will be inserted lateral to the surgical incision and placed in a way that the tip of the catheter is in the pelvic cavity and the opposite end brought out through the abdominal wall, lateral to the skin incision and fixed with dressing. Ten ml of the Ropivacaine 0.2% will be injected intermittently every other hour via an infusion pump (CADD-Solis) via a bacterial filter that will be programmed to administer an intraperitoneal infusion of 10 mL Ropivacaine 2mg/ml as a bolus injection every other hour for 72 h postoperatively. 72 hours after the end of the surgical procedure the intermittent infusion ends and the intraperitoneal catheter is removed. The amount of infused Ropivacaine 2mg/ml by intraperitoneal infusion will be recorded and the infusion bags discarded in a secure fashion.

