### 11.3 Clinical Safety Assessments

All side effects (nausea, vomiting, pruritus, respiratory depression, oxygen desaturation and need for supplementary oxygen) and complications related to anesthesia and/or surgery (bleeding, reoperation, pneumothorax etc.) will be recorded during the hospitalization according to standardized methods. Prolonged PACU stay or re-admission to PACU will be registered. Clavien-Dindo classification for grade of complication will be registered as also Postoperative Morbidity score (POMS).

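### Section 8.3 assigns safety data to a per-protocol approach and names no all-treated set, so rates of adverse events outside the secondary outcomes may be understated

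*Protocol*

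**What the plan says.** Protocol section 8.3 gives two rules on who is analysed. For efficacy: "All analyses of primary and secondary outcome will be performed according to the intention-to-treat principle but may also be presented as per-protocol". For safety: "For safety data, patients will be analyzed according to per-protocol approach". The safety rule carries no exception. The protocol neither defines the per-protocol set nor names an all-treated or as-treated set.

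Four other places bear on the rule.

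- **Treatment to be completed.** Section 5.1 describes three intraoperative doses, then a pump "programmed to administer an intraperitoneal infusion of 10 mL Ropivacaine 2mg/ml as a bolus injection every other hour for 72 h postoperatively".
- **Leaving the study.** Section 4.6 states: "The investigator/sponsor can at any time terminate the study for a subject due to, e.g., unacceptable adverse events/adverse reactions". Failure to follow study procedures is a second reason. The section then says: "If the subject discontinues the study, follow-up of this subject will be performed according to the clinic's routine".
- **What counts as an AE.** Section 12.1 ties an AE to having been given the study drug, not to completing the course.
- **What is a secondary outcome.** Section 8.2 lists: "Postoperative complications, postoperative morbidity, quality of recovery, cardiac and renal impairment and overall survival". These fall under the intention-to-treat rule. Section 11.3 also lists Clavien-Dindo and POMS among the items recorded for safety. Section 12.4.1 says that postoperative complications are recorded but are not analysed as AEs.

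**The concern.** A per-protocol set is normally built from women who received the treatment as planned. A woman whose course is cut short because of an adverse event does not meet that description. If she is left out, membership of the safety set depends on the outcome that the set is meant to measure.

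Section 9.1 describes toxicity that can occur at high doses, with neurological and cardiovascular signs, and a theoretical risk of catheter-related infection. These are plausible reasons for a 72 h infusion to end early, and events of this kind belong in the safety tables. The rule also sits badly with section 12.1, where exposure alone makes an event an AE.

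The protocol's case for the treatment rests partly on low toxicity (sections 9.1 and 13). The AE and SAE tables should therefore not be open to the criticism that the women with most to report were left out.

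**Working it through.** **Inputs.** The protocol gives no harm rate, no stopping rate and no safety power calculation, so there is no planned figure to reproduce. The only input taken from it is the arm size: 220 women allocated 1:1, or 110 per arm (sections 4.4 and 8.4). The risks p and the shares s below are assumptions.

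**Formula.** Let p be the true risk of an event in an arm, and s the share of affected women who stop treatment because of it and are therefore left out. The set keeps a fraction 1 − ps of the arm, and p(1 − s) of the arm still counts as events. Hence

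per-protocol risk = p(1 − s) / (1 − ps).

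**Assumed risks 5% (ropivacaine) and 1% (saline), same s in both arms. True difference 4.0 points.**

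| s | Ropivacaine | Saline | Difference |
|---|---|---|---|
| 50% | 0.025/0.975 = 2.56% | 0.005/0.995 = 0.50% | 2.06 points |
| 80% | 0.010/0.960 = 1.04% | 0.002/0.992 = 0.20% | 0.84 points |
| 100% | 0 | 0 | 0 |

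In counts, 110 × 0.05 = 5.5 ropivacaine events are expected, and at s = 80% only 5.5 × 0.2 = 1.1 remain.

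**Assumed risks 10% and 5%, same s. True difference 5.0 points.**

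| s | Ropivacaine | Saline | Difference |
|---|---|---|---|
| 25% | 7.69% | 3.80% | 3.9 points |
| 50% | 5.26% | 2.56% | 2.7 points |
| 75% | 2.70% | 1.30% | 1.4 points |
| 100% | 0 | 0 | 0 |

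**Unequal shares.** With 10% and 5%, s = 50% on ropivacaine and 25% on saline, the risks are 5.26% and 3.80%. The difference falls from 5.0 to 1.5 points and the risk ratio from 2.0 to 5.26/3.80 = 1.4.

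**No true excess.** With 10% in both arms and s = 50% in both, each rate falls to 5.3% and the difference stays at 0. With s = 50% on ropivacaine and 25% on saline, the difference is 5.26 − 7.69 = −2.4 points, a spurious advantage for ropivacaine.

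**When the direction holds.** For equal s, the slope of the formula in p is (1 − s)/(1 − ps)². It is below 1 for p up to 50%, because (1 − ps)² exceeds 1 − 2ps, which is then at least 1 − s. A true excess therefore shrinks. The formula falls as s rises, so a larger s on ropivacaine lowers the difference further. If s were larger on saline, the difference could grow: 5% and 1% with s = 0 and 50% gives 5.0 − 0.5 = 4.5 points.

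**The case against.** The strongest reply is that the harm comparison is largely protected already. Complications, morbidity and cardiac and renal impairment are secondary outcomes under intention to treat, with chi-square tests and, for dichotomous outcomes, confidence intervals for differences in proportions. An arrhythmia can enter the cardiovascular item of POMS and a catheter infection the infectious item. Clavien-Dindo grade I is broad and runs to day 30. This stands, and it confines the problem to AEs, SAEs and side effects outside those outcomes. Because section 12.4.1 separates complications from AEs, the complication analysis does not replace the AE and SAE tables.

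Second, the per-protocol set is undefined. The authors may have meant treatment received, and an SAP may define the set. Section 4.6 concerns ending participation. It mentions neither stopping the infusion nor discarding data already collected. This also stands, so the loss of harmed women is a consequence of the usual meaning of the term, not something that the protocol states. It does not rescue the sentence: on the usual meaning the rule is biased, and on the generous reading the term is wrong. An SAP with an all-treated set would contradict 8.3.

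Third, the rates are assumed, and shares of 80% or 100% are extreme. Section 9.1 reports no sign of systemic toxicity in the earlier 40-patient study. With equal shares the risk ratio barely moves (5.0 against 1.04/0.20 = 5.2). The size is therefore illustrative only.

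A reader might also infer that Clavien-Dindo and POMS have two conflicting analysis sets, because section 11.3 lists them for safety. The documents do not support this. Section 11.3 concerns recording, while 8.3 places every secondary-outcome analysis under intention to treat. It is an overlap in wording that one clause settles.

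**Conclusion.** The safety rule in section 8.3 should be changed. It names a population which, in its usual meaning, is selected partly on harm. It does not fit the exposure-based AE definition in 12.1, and no all-treated set stands beside it.

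The conclusion is conditional. If women who stop because of an event are left out, AE, SAE and side-effect rates are understated. A true excess risk difference on ropivacaine also shrinks, provided that risks do not exceed 50% and the share dropped is equal in both arms or larger on ropivacaine. Under the assumed 5% and 1%, 4.0 points become 2.1 at a share of 50% and 0.8 at 80%. The actual size cannot be derived from the protocol.

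A reader might infer that all safety data are affected, or that the trial could declare ropivacaine safe merely through the choice of set. That goes too far, because the main complication, morbidity and organ-impairment comparisons are by intention to treat.

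**What to change.** Replace the safety sentence in section 8.3 with:

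> Safety data (AEs, SAEs, side effects) will be analysed in all women who received any amount of study drug, according to the treatment actually received, whether or not the 72 h course was completed. A per-protocol display may be added as a supplement.

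Add two clarifications.

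1. The safety set includes women who were given Dose 1 and were then excluded because no cytoreduction was attempted (sections 4.3 and 6). Dose 1 is given before dissection, so these women have been exposed.
2. Clavien-Dindo and POMS, although also listed in section 11.3, stay under intention to treat as secondary outcomes.

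The cost is a few sentences in 8.3, carried into any SAP. It needs no additional patients and changes no clinical procedure. Events already recorded for women who stopped early, and for those excluded after Dose 1, must be kept in the safety tables. The reported harm rates may look slightly less favourable as a result.
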